# Randomised controlled trial comparing the clinical and cost-effectiveness of various washout policies versus no washout policy in preventing catheter associated complications in adults living with long-term catheters: study protocol for the CATHETER II study

**DOI:** 10.1186/s13063-022-06577-2

**Published:** 2022-08-04

**Keywords:** Catheter blockage, Catheter washout solutions, Catheter maintenance solutions, Indwelling catheter, Long-term catheter, Symptomatic catheter-associated urinary tract infection

## Abstract

**Background:**

Various washout policies are widely used in adults living with long-term catheters (LTC). There is currently insufficient evidence on the benefits and potential harms of prophylactic LTC washout policies in the prevention of blockages and other LTC-related adverse events, such as urinary tract infections. CATHETER II tests the hypothesis that weekly prophylactic LTC washouts (normal saline or citric acid) in addition to standard LTC care reduce the incidence of catheter blockage requiring intervention compared to standard LTC care only in adults living with LTC.

**Methods:**

CATHETER II is a pragmatic three-arm open multi-centre superiority randomised controlled trial with an internal pilot, economic analysis, and embedded qualitative study. Eligible participants are adults aged ≥ 18 years, who have had a LTC in use for ≥ 28 days, have no plans to discontinue the use of the catheter, are able to undertake the catheter washouts, and complete trial documentation or have a carer able to help them. Participants are identified from general practitioner practices, secondary/tertiary care, community healthcare, care homes, and via public advertising strategies. Participants are randomised 1:1:1 to receive a weekly saline (0.9%) washout in addition to standard LTC care, a weekly citric acid (3.23%) washout in addition to standard LTC care or standard LTC care only. Participants and/or carers will receive training to administer the washouts. Patient-reported outcomes are collected at baseline and for 24 months post-randomisation. The primary clinical outcome is catheter blockage requiring intervention up to 24 months post-randomisation expressed per 1000 catheter days. Secondary outcomes include symptomatic catheter-associated urinary tract infection requiring antibiotics, catheter change, adverse events, NHS/ healthcare use, and impact on quality of life.

**Discussion:**

This study will guide treatment decision-making and clinical practice guidelines regarding the effectiveness of various prophylactic catheter washout policies in men and women living with LTC. This research has received ethical approval from Wales Research Ethics Committee 6 (19/WA/0015).

**Trial registration:**

ISRCTN ISRCTN17116445. Registered prospectively on 06 November 2019

**Supplementary Information:**

The online version contains supplementary material available at 10.1186/s13063-022-06577-2.

## Administrative information

Note: The numbers in curly brackets in this protocol refer to SPIRIT checklist item numbers. The order of the items has been modified to group similar items (see http://www.equator-network.org/reporting-guidelines/spirit-2013-statement-defining-standard-protocol-items-for-clinical-trials/).

## Introduction

### Background and rationale {6a}

Long-term catheters (LTC) are used by patients with conditions such as intractable urinary incontinence or chronic urinary retention to empty the bladder. Chronic urinary retention can be secondary to a variety of conditions such as enlarged prostate, underactive bladder, and neurological conditions such as spinal cord injury and multiple sclerosis [1, 2]. The National Institute for Health and Care Excellence (NICE) CG139 recommends an indwelling catheter for those who are unable to perform intermittent catheterisation or those for whom toileting is difficult [3]. The indwelling catheter may be inserted into the urinary bladder via the urethra (urethral catheter) or via the anterior abdominal wall (suprapubic catheter). The urine is either drained into a catheter bag or emptied when convenient with the use of a catheter valve. Current NHS standard care includes a change of the catheter bag or valve every week by the patient, or carer, and a change of the catheter every 4–12 weeks by the clinical team [4].

There is no robust evidence to support a definition for the duration of catheter stay that constitutes “long-term” catheter use. Evidence from a Cochrane review [2] indicate that most studies defined LTC use as urethral or supra-pubic catheter in situ for > 28 days with predicted use over 6–12 months. This definition was also used in the NICE CG139 [3]. LTC use may be for many years, Wilde et al. [5] reported a mean duration of six years in 202 participants (median 3.25 years).

The exact prevalence of LTC use is not known. It was estimated that between 0.2–0.5% of the general population of the United Kingdom (UK) are living with a LTC (unpublished data, [name], [name], 2018; personal communication, NIHR Clinical Research Network, NHS Research Scotland Primary Care Network). New evidence estimates the prevalence in the UK at approximately 90,000 LTC users (or 0.14% of the overall population) [6]. It is anticipated that LTC use will continue to increase with the increasing ageing population [7].

LTC can be associated with several adverse events [5] which affect the daily life of patients and can consume substantial NHS resources [8]. Wilde et al. reported typical adverse events of LTC blockage (34% of participants): symptomatic catheter-associated urinary tract infections (S-CAUTI), whether or not this has been proven bacteriologically (57%); accidental dislodgment (28%); urinary leakage (67%); bladder spasms (59%); kinks/twists (42%) and pain (49%) [1].

LTC blockages often occur secondary to the formation of encrustations on the luminal and outer surfaces of the catheter, with an incidence of 40–50% in patients in most studies [7, 9–11]. Wilde et al. in 2017 [1] assessed 202 patients with LTC over 12 months and showed that 34% of patients reported blockage and a rate of 8.54/1000 days of catheter use. Catheter blockage is considered a medical emergency and can lead to distress, autonomic dysreflexia in patients with spinal cord injury at or above T6, increased healthcare utilisation and urosepsis [12]. Current best practice for the management of LTC blockage requires a regular (and more frequent) change of the catheter [3]. Catheter washouts are often used in these cases despite the lack of evidence on their benefit, potential harm, best solution to be used, appropriate volume and frequency, and individual impact on quality of life among patients with LTC [2].

Several catheter washouts policies are used in clinical practice for the prevention and/or management of LTC blockage. Washouts used are of different types (normal saline, acidic, antimicrobial), volumes and frequency of administration. The Cochrane review [2] assessed the best available evidence and concluded that there is insufficient evidence to determine whether prophylactic catheter washout policies had a beneficial or harmful effect on any of the outcomes in patients with LTC. The authors recommended a rigorous and methodologically robust randomised controlled trial to assess the clinical and cost-effectiveness of washout policies in patients with LTC.

Muncie et al. [13] compared saline washouts versus no washouts policy over 24 weeks in a limited population and showed no significant differences in S-CAUTI per 100 days of catheter use. Concerns exist that the use of washouts can damage the bladder mucosa and possibly increase the risk of S-CAUTI. NICE CG139 recommend that “[catheter] washouts must not be used to prevent catheter-associated infections” [3].

In CATHETER II, researchers will evaluate what is the clinical and cost-effectiveness, patient acceptability and satisfaction, and safety of weekly prophylactic catheter washout policies in addition to standard LTC care compared to standard LTC care only, in adults living with LTC.

### Objectives {7}

The aim of the study is to determine whether the addition of a policy of prophylactic weekly catheter washouts to current standard LTC care improves the outcome of care for people living with a LTC in the UK.

The hypotheses being tested are:Does a policy of weekly prophylactic normal saline catheter washouts plus standard LTC care result in a relative reduction of 25% (or more) in catheter blockage requiring intervention compared to standard LTC care alone?Does a policy of weekly prophylactic acidic catheter washouts plus standard LTC care result in a relative reduction of 25% (or more) in catheter blockage requiring intervention compared to standard LTC care alone?

### Trial design {8}

CATHETER II is a pragmatic three-arm, parallel-group, open multi-centre superiority randomised controlled trial. It compares the clinical and cost-effectiveness, patient acceptability and satisfaction, and safety of weekly prophylactic catheter washouts policies in addition to standard long-term catheter (LTC) care compared to standard LTC care only, in adults living with LTC.

## Methods: participants, interventions and outcomes

### Study setting {9}

Participants are recruited from general practitioner (GP) practices, secondary and tertiary care hospitals, community hospitals and care homes including nursing homes in Scotland, England and Wales. Participants are also recruited via a public advertising strategy such as on websites and social media platforms, utilising targeted advertisements. A list of current study sites can be obtained from the CATHETER II study website [14].

### Eligibility criteria {10}

The inclusion criteria are:Aged ≥ 18 yearsCatheter has been in use for ≥ 28 daysNo plan for discontinuation of LTC at the time of recruitmentAble to undertake catheter washouts or has a designated person (relative, friend, other informal carer or paid/NHS healthcare worker) able to perform washoutsAble to complete the trial documentation or has a designated person able to assist with trial documentationAny type and route of LTC can be included

The exclusion criteria are:Intermittent self-catheterisationPregnant or contemplating pregnancySpinal cord injury at or above the sixth thoracic vertebra (T6) (risk of autonomic dysreflexia)Ongoing S-CAUTI (until treatment is complete)Visible haematuria (unless investigated/ treated)Known allergies to either of the catheter washout solutionsCurrent bladder cancer (until treatment is complete and patient discharged from cancer surveillance programme)Known bladder stones (until treatment is complete)Unable to provide consent due to incapacityAny other clinical and social reasons that would be deemed by the recruitment team to be unsuitable for the study

### Who will take informed consent? {26a}

Written informed consent from participants is sought and obtained by delegated Good Clinical Practice (GCP) trained members of the local research team. Consent may be sought during a face-to-face appointment, or participants may have the consent discussion with a member of the research team by telephone, and then return their completed consent form by post for countersignature by the member of the team who had had the consent discussion with the participant. If a potential participant with the capacity to consent is unable to provide written consent due to a physical incapacity, an impartial witness will witness the oral consent process and sign the study consent form on the participant’s behalf. If the participant requires help from a designated person (relative, friend, other informal carers) to carry out the washouts or to assist with trial documentation, written consent is sought from the designated person for the relevant activities by a GCP-trained member of the local research team. Written or verbal consent to participate in the qualitative interview study is obtained separately from participants and healthcare professionals by a GCP-trained qualitative researcher. All consent is taken in accordance with the GCP guidelines.

### Additional consent provisions for collection and use of participant data and biological specimens {26b}

Participants can opt in to be contacted about participating in future relevant research. No biological specimens are collected in CATHETER II.

### Interventions

#### Explanation for the choice of comparators {6b}

Uro-Tainer® Twin SUBY G and Uro-Tainer® NaCl 0.9% CE 100 ml are the most commonly used catheter washout solutions in the UK (correspondence, B.Braun Medical AG) and have been provided gratis for the study by the manufacturer. We are comparing these against standard LTC care (i.e. with no planned prophylactic LTC washouts).

#### Intervention description {11a}

The interventions being compared are:*Intervention arm (A):* Saline washouts. A policy of weekly prophylactic normal saline catheter washouts plus standard LTC care. One application of 100 ml 0.9% NaCl per washout (Uro-Tainer® NaCl 0.9% CE)*Intervention arm (B):* Acidic washouts. A policy of weekly prophylactic acidic catheter washouts plus standard LTC care. Two sequential applications of 30 ml 3.23% citric acid per washout (Uro-Tainer® Twin SUBY G)*Control arm (C):* Standard LTC care only with no prophylactic catheter washout

Washouts are administered in accordance with best practice technique at the time of the regular weekly catheter bag or valve change, to reduce the risk of introducing infection by minimising the breakage of the closed drainage system. Participants and/or their relatives, friends, or other informal carers will receive training to administer catheter washouts from an appropriately trained member of the local study team to enable them to self-administer the washouts in accordance with best practice. Training is provided with either face-to-face or by video/phone consultation and is supported with an online training video and hardcopy instructions for use with troubleshooting advice. If a health professional usually changes the catheter bag or valve for a participant and capacity and capability allows, they will be asked to undertake training and perform the washout within the study. The washouts are couriered directly to the participant from the trial office.

#### Criteria for discontinuing or modifying allocated interventions {11b}

Washout use is discontinued if a participant stops using the LTC for 28 days or longer, or if they no longer wish to carry out regular washouts, or if they are unable to carry out the washouts following training, or if they withdraw consent for the monthly data collection schedule and decline for this information to be collected less frequently. Where deemed clinically necessary by the clinical team, the pragmatic design of the study permits the following changes to washout policies:An increase in the frequency of LTC washouts, at the onset of the study or following regular review during the course of the studyA change in the type of washout, at the onset of the study or following regular review during the course of the studyThe use of prophylactic washouts in the control arm, following regular review during the course of the study (but not at the onset of the study)

#### Strategies to improve adherence to interventions {11c}

The site team ask the participant about adherence at every monthly contact, and this is recorded in the case report form (CRF). We would expect at least 80% of participants to be undertaking 60% of their washouts and this is monitored during the internal pilot phase. If the threshold is not met, we may consider adapting or offering participants more training sessions.

#### Relevant concomitant care permitted or prohibited during the trial {11d}

Standard catheter care is permitted during the trial and managed by the participant’s usual health care team. The use of prophylactic washout solutions in the standard care arm is discouraged at the onset of the study. There is no change to other care received by the participant.

#### Provisions for post-trial care {30}

At the conclusion of the study, no further washout solutions will be sent to participants by the trial team, and they will continue their care and treatment in line with standard NHS clinical care.

### Outcomes {12}

The primary clinical outcome is catheter blockage requiring intervention up to 24 months post-randomisation expressed as number per 1000 catheter days.

Intervention is defined as any of the following: unplanned catheter removal or change or washout performed by the participant/designated person or required unplanned visits to/from any healthcare provider, or hospital admission.

The primary economic outcome is the incremental cost per quality-adjusted life year gained for each washout policy compared to standard LTC care only.

Secondary outcomes include:S-CAUTI requiring antibiotics use (as defined by Pickard et al. [15])Duration of LTC in use, catheter change due to other reasons than blockageAdverse events;Hospital admissions, GP/nurse outpatient visits for catheter-related complicationsGeneric quality of life as assessed by EQ-5D-5L [16] (EuroQol Questionnaire – 5 Dimensions – 5 Levels)Condition-specific quality of life assessed by ICIQ-LTCqol [17] (International Consultation on Incontinence Modular Questionnaire – Long Term Catheter quality of life)Adherence to allocated interventionsPatients’ convenience and satisfaction assessed by an adapted version of the abbreviated Treatment Satisfaction Questionnaire for medication [18]Impact on day-to-day activities using the General Self-Efficacy Scale (GSE) [19] and ICECAP-A (ICEpop CAPability measure for Adults) (≤ 65 years) or ICECAP-O [20] (ICEpop CAPability measure for Older people) > 65 yearsTime and travel costs for patients and their relatives, friends or informal carersDiscontinuation of catheter useEvents changing the type and/or frequency (or cessation) of catheter washouts in arms A and B and rates of commencing on prophylactic washouts in arm C

Qualitative study outcomes:Participants’ experience of LTC-related adverse events such as blockage, S-CAUTI, urinary incontinence and bladder pain.Participants’ attitudes/preferences to washout versus no washout policies and expected outcomes (prior to randomisation or knowing their allocated study group) (acceptability).Participants’ experience with washout/no washout policies and evaluation of outcomes (satisfaction).Clinicians’ attitudes towards the influence of washout policies on outcomes.Participants’ and clinicians’ experience of training provided and enactment of the treatment skill. This would clarify the fidelity of the intervention.

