### Assignment of interventions: blinding

#### Who will be blinded {17a}

It is not possible to blind the allocated study arm.

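### Counting a washout done at home as a primary event may lower the threshold for recording minor blockages in arms A and B, and needs a two-sided sensitivity check

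*Protocol article*

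**What the plan says.** Under Outcomes {12} the primary outcome is blockage requiring intervention, per 1000 catheter days. The rule for what counts opens with "Intervention is defined as any of the following", so one route is enough. The routes are "unplanned catheter removal or change or washout performed by the participant/designated person or required unplanned visits to/from any healthcare provider, or hospital admission".

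Under Intervention description {11a}, participants or their informal carers "will receive training to administer catheter washouts from an appropriately trained member of the local study team", and "The washouts are couriered directly to the participant from the trial office". Neither sentence names an arm, but both describe how the washout policy is delivered. Control is defined as "Standard LTC care only with no prophylactic catheter washout".

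On blinding, {17a} says "It is not possible to blind the allocated study arm". Under {18a}, events are written in a diary by the participant, the carer or the research team, and collected about monthly.

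Other sections bear on washouts in control. The background says of blockage that "Catheter washouts are often used in these cases despite the lack of evidence on their benefit". Every entrant must be able to do washouts or have someone who can {10}. The restriction in {11d} is narrow: "The use of prophylactic washout solutions in the standard care arm is discouraged at the onset of the study". Under {11b}, control participants may start prophylactic washouts after review.

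**The concern.** One route into the primary outcome is the same act as the treatment under test. On a plain reading, arms A and B are trained and supplied for it by the trial from the start, and control is not. Suppose drainage slows or a blockage is suspected. In arm A or B the participant may do a washout, and the episode counts with no healthcare contact. In control the same episode may clear without any listed intervention and never count. The article gives no definition of blockage that is independent of the action taken, and there is no blinding to even out the recording.

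The wording leaves a second gap. It is unclear whether the word unplanned governs only removal or change, or the washout as well. If it does not reach the washout, a scheduled weekly washout that happens to clear sluggish flow could be counted, and scheduled washouts are assigned only to A and B.

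At stake is what the rate ratio means. It would combine the effect of washouts on blockage with an effect on how readily a minor blockage is recorded. The second part would run against washouts, so it could mask a benefit or suggest a harm.

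**Working it through.** **Inputs from Sample size {14}.** Control rate r0 = 11.8 and washout rate r1 = 8.9 per 1000 days (ratio 8.9/11.8 = 0.754); dispersion k = 0.6; follow-up t = 730 − 50 = 680 days; n = 200 per arm; 90% power; significance level 2.5%, sidedness not stated.

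**Step 1: reproduce the plan's figure.** The formula for two negative binomial rates, with the null variance set equal to V, is

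n = (z_a + z_b)² V / (ln RR)², with V = (1/t)(1/r0 + 1/r1) + 2k.

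- V = (84.75 + 112.36)/680 + 1.2 = 1.490, and ln 0.754 = −0.282.
- One-sided 2.5%: (1.960 + 1.282)² × 1.490 / 0.282² gives 197 per arm. Other choices of null variance give 194 to 197. This agrees with 200.
- Two-sided 2.5%: z_a = 2.241 gives 233 per arm (229 to 233). This does not agree with 200.

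Power at n = 200 is Φ(|ln RR|/SE − z_a), with SE = √(V/200) = 0.0863. That is Φ(3.27 − 1.96) = 90% one-sided and Φ(3.27 − 2.24) = 85% two-sided. Both are carried below, because the point does not depend on which was meant.

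**Step 2: extra events counted in a washout arm.** Let a washout arm record a fraction f of additional minor episodes that control would not record, so r1 becomes 8.9 × (1 + f). The documents give no value for f, and zero is possible. The values below are assumptions.

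| f | Ratio seen (true 0.754) | Power, two-sided 2.5% | Power, one-sided 2.5% |
|---|---|---|---|
| 0 | 0.754 | 85% | 90% |
| 5% | 0.79 | 68% | 77% |
| 10% | 0.83 | 47% | 58% |
| 15% | 0.87 | 28% | 38% |

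Worked row, f = 10%: r1 = 9.79, ratio 0.830, ln = −0.187, V = 1.475, SE = 0.0859. Then 0.187/0.0859 = 2.17, which is just short of 2.24 and just above 1.96.

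With no true effect (ratio 1), the chance of a significant result in the direction of harm at two-sided 2.5% is 5, 13 or 28% for f = 5, 10 or 15%. The nominal figure is 1.25% in that tail.

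**Step 3: how many episodes that is.** At the planned rate a washout participant has 8.9 × 0.68 = 6.05 events in 680 days. So f = 5, 10 or 15% means 0.30, 0.61 or 0.91 extra counted episodes per participant. The weekly schedule gives 680/7 = 97 washouts over the same time. This sets the scale and does not show that such episodes occur.

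**Step 4: the opposite error.** Now drop self-washout-only episodes from the count. If there is no true effect and 10% of real blockages in a washout arm are cleared at home and so dropped, while the matching control blockages led to a visit and stay in, the ratio seen is 0.90. The chance of a false benefit at two-sided 2.5% is then 16%. At 15% dropped, the ratio is 0.85 and the chance is 36%. These fractions are also assumptions.

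**The case against.** The strongest reply is that the self-washout route protects comparability. The background treats blockage as an emergency. A control participant with a real blockage will have a catheter change, an unplanned visit or an admission, and each counts. Without the washout route, the same blockage cleared at home in A or B would be lost, and the comparison would favour washouts. This stands. It limits the concern to minor or suspected blockages that would not otherwise have led to a listed intervention.

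A reader might infer that only A and B can reach this route. The documents do not say so. Control participants or their helpers must be able to do washouts, usual care often uses them for blockage, only prophylactic use is discouraged and only at the start, and control may begin washouts after review. A reactive self-washout in control is possible and would count. Nor is it stated that A and B hold kits beyond the weekly supply. This too stands: it dilutes the imbalance, although being able to do a washout is not the same as being trained and supplied by the trial.

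A further reply is that analyses by component belong in the statistical analysis plan, which is not shown and may contain one. That is fair for the sensitivity analysis. It does not settle the outcome wording, which the protocol itself fixes. The secondary outcomes on admissions and GP or nurse visits overlap with the routes, but they cover catheter-related complications in general and do not isolate blockages counted through a home washout alone.

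**Conclusion.** The concern holds in a limited form. The threshold for counting minor blockages may be lower in A and B than in control, and if so the bias runs against washouts. The documents do not support the stronger statement that event counting does differ by arm: blockages needing action count everywhere, and control is not shown to lack washouts. They also do not support treating a count without self-washouts as neutral between arms, since Step 4 shows it errs the other way by a similar amount.

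The size is unknown. On the assumed 5 to 15% excess, the planned ratio of 0.754 would be seen as 0.79 to 0.87, and power would fall to between 68 and 28% (two-sided) or 77 and 38% (one-sided). These figures rest on the planning rates, k = 0.6, 680 days and 200 per arm. A small excess would be enough to matter, and without the type of intervention for each blockage the trial could not tell whether it occurred.

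**What to change.** Keep the primary outcome and make four additions.

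1. State in the outcome definition that a washout counts only if it was unplanned and done in response to a blockage, so that scheduled washouts do not qualify.
2. Record the type or types of intervention for every blockage at the existing monthly contact.
3. Report by arm the number of blockages counted through a self-washout alone.
4. Pre-specify, for both comparisons with control, a sensitivity analysis that fits the same negative binomial model without those episodes.

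Present the sensitivity result beside the primary one as a bracket. The primary may lean against washouts; the restricted count leans towards them because it drops real blockages cleared at home in A and B. It should not be called arm-neutral or decide the trial's conclusion. If the two analyses disagree, qualify the conclusion. The bracket rests on the two biases running in the directions described, which the by-arm counts will help to judge.

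The cost is a sentence in the outcome definition, one item on the monthly form if it is not already there, and one repeat of the model per comparison. The downsides are fewer events in the narrower count and its opposite bias. The form item is the urgent part, because the type of intervention cannot be reliably recovered after 24 months.

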### Assignment of interventions: allocation

#### Sequence generation {16a}

Participants are allocated 1:1:1 to one of the three trial arms by a member of the local research team using a centralised computerised randomisation system (administered by the Centre for Healthcare Randomised Trials (CHaRT), University of Aberdeen. Random allocation uses the minimisation covariates: region; gender; age (< 45 years, 45–64 years and ≥ 65 years); residential status (care home vs community); previous blockages requiring intervention in the last 6 months (0 vs ≥ 1); previous S-CAUTI requiring antibiotics in last 6 months (0 vs ≥ 1); Urine pH (normal vs acidic vs alkaline vs not available).

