#### Methods for additional analyses (e.g. subgroup analyses) {20b}

The following subgroup analyses are planned:Women vs menNeuropathic bladder vs. non-neuropathic bladderAge groups: < 45 vs. 45–64yrs vs. > 65Participants with no history of LTC blockages versus those with recurrent blockagesParticipants with no history of S-CAUTI vs those with recurrent S-CAUTIParticipants with baseline urinary pH: normal range vs alkaline vs acidic

All subgroup analyses will be at the 99% significance level.

An economic evaluation is integrated into the trial and includes both a trial-based analysis and a modelling exercise to extrapolate the results over the patient’s lifetime. Outcomes and costs are assessed from the perspective of the NHS and patients. Effectiveness is measured in terms of quality-adjusted life years gained.

Qualitative interview and focus group transcripts will be analysed using an explicit, structured qualitative method of thematic analysis.

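### The primary economic outcome sets each washout against standard care; those ratios alone do not rank three competing policies, and a fully incremental definition would do so at little cost

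*Protocol article*

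**What the plan says.** The protocol article, Outcomes {12}, defines the outcome in one sentence: "The primary economic outcome is the incremental cost per quality-adjusted life year gained for each washout policy compared to standard LTC care only". The last word belongs to the name of the control arm, but standard care is still the only comparator named.

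Intervention description {11a} lists three policies: "A policy of weekly prophylactic normal saline catheter washouts plus standard LTC care", "A policy of weekly prophylactic acidic catheter washouts plus standard LTC care" and "Standard LTC care only with no prophylactic catheter washout". Sequence generation {16a} makes them parallel alternatives: "Participants are allocated 1:1:1 to one of the three trial arms".

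The economic methods appear briefly under Methods for additional analyses {20b}: "An economic evaluation is integrated into the trial and includes both a trial-based analysis and a modelling exercise", the model running over a lifetime, with an NHS and patient perspective and QALYs as the effect measure. That section does not say how the three arms are to be compared. Objectives {7} and the choice of comparators {6b} also set each washout against standard care.

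On purpose, Background and rationale {6a} describes a "lack of evidence on their benefit, potential harm, best solution to be used", among other gaps. The Discussion paragraph of the Abstract says: "This study will guide treatment decision-making and clinical practice guidelines regarding the effectiveness of various prophylactic catheter washout policies".

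**The concern.** When options exclude one another, the ratio that bears on the dearer and more effective one is its extra cost per extra QALY over the next-best option that is not dominated. Here that option may be the other washout. A ratio against a shared baseline averages over the whole distance from standard care and can hide a poor last step.

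Two such ratios can therefore both look acceptable when only one policy maximises net benefit. They can also make a dominated washout look reasonable. Nor is the smaller ratio always the better choice. If both washouts look worthwhile, a reader who wants to know which to adopt does not get the answer from the outcome as defined, although the choice of solution is one of the gaps that motivate the trial.

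The article states this comparison structure positively. It is not a detail merely left out, and an economic analysis plan that follows the definition would inherit it.

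**Working it through.** **Inputs.** The article gives no cost, QALY difference, ratio or willingness-to-pay threshold, so there is no figure to reproduce. All values below are assumptions: thresholds of £20,000 and £30,000 per QALY, and small cost and QALY differences from standard care. The labels W1 and W2 stand for the two washouts in either order; nothing here predicts which is which.

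**Formulas.** With ΔC and ΔQ measured against standard care and λ the threshold:
- ratio against standard care = ΔC / ΔQ
- step from W1 to W2 = (ΔC2 − ΔC1) / (ΔQ2 − ΔQ1)
- net monetary benefit (NMB) = λ × ΔQ − ΔC, with standard care at 0

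**Results.**

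| Case | W1: ΔC, ΔQ, ratio | W2: ΔC, ΔQ, ratio | Step W1 to W2 | NMB at £20,000 (W1; W2) | NMB at £30,000 (W1; W2) |
|---|---|---|---|---|---|
| a | £300, 0.030, £10,000 | £700, 0.036, £19,444 | 400/0.006 = £66,667 | £300; £20 | £600; £380 |
| b | £200, 0.020, £10,000 | £450, 0.025, £18,000 | 250/0.005 = £50,000 | £200; £50 | £400; £300 |
| c | £300, 0.030, £10,000 | £500, 0.025, £20,000 | W2 dominated | £300; £0 | £600; £250 |
| d | £200, 0.020, £10,000 | £500, 0.030, £16,667 | 300/0.010 = £30,000 | £200; £100 | £400; £400 |
| e | £200, 0.020, £10,000 | £600, 0.035, £17,143 | 400/0.015 = £26,667 | £200; £100 | £400; £450 |

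Example of the net benefit arithmetic, case a at £20,000: W1 gives 20,000 × 0.030 − 300 = 600 − 300 = £300; W2 gives 20,000 × 0.036 − 700 = 720 − 700 = £20.

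**Reading the cases.**
1. In cases a and b both ratios against standard care are below £20,000, yet the step to W2 exceeds both thresholds and W1 has the higher net benefit at each.
2. In case c, W2 costs more and gains less than W1, but its ratio against standard care is only £20,000. That ratio alone does not reveal the dominance.
3. In case d the step equals £30,000, so the two washouts tie at that threshold, and W1 is preferred at £20,000.
4. In case e the step is too dear at £20,000 but acceptable at £30,000. At £30,000 W2 is the better choice (30,000 × 0.035 − 600 = £450 against 30,000 × 0.020 − 200 = £400) although its ratio against standard care is the larger. Choosing the smaller ratio would be wrong there.

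The pairwise ratios thus fail to settle the choice in either direction, and whether this matters in practice depends on figures the trial has yet to produce.

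**The case against.** The strongest reply is that an outcome definition is not a decision rule. The article sets no threshold and does not say that every washout with an acceptable ratio will be recommended. A reader might infer that the plan, if followed, would endorse the wrong policy; the text does not support that, because the adoption rule and the threshold come from the illustration. This stands, and it limits the weight of the point.

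Second, nothing is lost in the data. The step ratios and net benefits above were all obtained from differences against standard care. If those cost and QALY differences are reported, all three arms can be ranked; only ratios shown without them obscure the order. This also stands, and it is why the remedy is cheap.

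Third, the article condenses a longer protocol, which Plans to give access {31c} says is available elsewhere, and an economic analysis plan may exist. A reader might infer that no saline-versus-acidic comparison is planned at all. That cannot be established from this text: dominance rules and acceptability curves are commonly left to the longer documents, and the single regression described under Statistical methods {20a} could yield the clinical contrast. What remains is narrower: the comparator named in the published outcome definition.

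Fourth, the definition agrees with the two hypotheses under Objectives {7}, each against standard care. It does, so there is no internal contradiction. But those hypotheses concern blockage. A value-for-money question among three exclusive options has a different structure, and agreement with the clinical hypotheses does not make the pairwise ratios sufficient for it.

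**Conclusion.** The point holds as a worthwhile improvement to how the primary economic outcome is defined. As stated, it is a pair of ratios on a common baseline for three mutually exclusive policies, and such ratios do not by themselves identify the best one. The illustrations show both washouts passing £20,000 per QALY while the step between them costs £50,000 to £66,667, or while one is dominated; they also show inputs under which the step is acceptable at £30,000.

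That range rests wholly on assumed costs, QALYs and thresholds. It shows what can happen, not how likely it is. Randomisation, sample size, data collection and the primary clinical outcome are unaffected, and the trial is not invalidated. The unseen economic plan may already contain the fuller analysis; in that case only the published definition needs to be brought into line.

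**What to change.** Redefine the primary economic outcome as a fully incremental comparison of the three arms:
- order the arms by mean cost, remove dominated and extendedly dominated options, and give each remaining ratio against the next-best option;
- report net monetary benefit and the probability of being cost-effective for all three arms together, over a stated range of thresholds;
- apply the same rule to the trial-based analysis and the lifetime model;
- report the acidic-versus-saline difference in cost and in QALYs, with its interval;
- keep the two ratios against standard care as supporting results.

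The cost is a change of wording in the outcome definition and, if needed, in the economic analysis plan. It uses the same data and models, with no extra participants or visits. It is best done before results are known, so that the choice of comparator cannot appear to follow from them.
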